## Methods/design

Our comparative case study will use mixed methods and will be guided by the Knowledge to Action Framework [35, 36]. Following Yin’s approach, the cases will be bound by location (prostate cancer clinical pathway at one hospital in one provincial health system and the prostate cancer surgical pathway in another province) and time period (2 years after PtDA implementation) [37]. The Knowledge to Action framework focuses on specific implementation factors essential for success in real world, naturalistic environments [35, 36]. The Action Cycle was activated by a problem identified by the knowledge users (e.g., men want to be more involved in prostate cancer decisions), and the knowledge solution is a PtDA. Then, we will identify interventions to overcome identified barriers. This proposed implementation study is focused on the final phases of the Framework: monitor use, evaluate outcomes, and measure sustained use. Sustainability requires monitoring use for 2 or more years [38]. We obtained ethics approval at The Ottawa Health Science Network Research Ethics Board (#20150604-01H), the Saskatoon Health Region Research Ethics Board (#BEH-15-382), Reginal Qu’Appelle Health Region Research Ethics Board (REG-15-125), and the University of Saskatchewan Behavioural Research Ethics Board (BEH#15-382).

The *setting* for our study is prostate cancer healthcare services that implemented PtDAs in the clinical pathways: The Ottawa Hospital in Ontario (in 2010) and the Ministry of Health in the Province of Saskatchewan (in 2013). These prostate cancer healthcare services have urologists and radiation oncologists serving populations of about 1 million each. Annually, about 400 men have consultations for prostate cancer at The Ottawa Hospital Cancer Assessment Clinic and about 600 in Saskatchewan. Within the clinical pathway, men diagnosed with localized prostate cancer are asked to use the PtDA at home in preparation for the consultation. Nurses, trained in interprofessional shared decision-making [31], discuss men’s questions prior to the physician consultation.

*Participants* for the interviews are men who have received a diagnosis of localized prostate cancer (including their partners) and received services at The Ottawa Hospital or in Saskatchewan. Other stakeholder participants who have varying levels of influence in the prostate cancer programs include urologists, radiation oncologists, nurses, and managers.

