### Analysis

Two cases will be developed with a rich description of the context and outcomes with comparisons within and across the cases [37]. For PtDA use, the proportion of men given the PtDA will be calculated for each site with 95 % confidence intervals (Table 1). We anticipate about 600 men diagnosed with localized prostate cancer over 2 years at The Ottawa Hospital Cancer Assessment Clinic and 400 in the Provincial Prostate Pathway in Saskatchewan. Using conservative estimates for proportions given the PtDA of 50 and 90 % in Ottawa and Saskatchewan, respectively, these sample sizes are adequate to estimate the true proportions given the PtDA with margins of error +4.0 % in Ottawa and +2.9 % in Saskatchewan using two-sided 95 % confidence intervals. Characteristics and outcomes of patients who did and did not receive the PtDA will be described at each site using mean and standard deviation for continuous variables, and frequencies and proportions for categorical variables.

Factors associated with receiving the PtDA will be explored at each site and overall using multivariable logistic regression analysis by entering patient characteristics (e.g., age, co-morbidity, severity of disease, cancer characteristics) as well as provider characteristics (e.g., sex, years of experience, discipline). To explore differences in the effect of these characteristics across the two sites, site and interactions between the characteristics and site will be included in the model. If the proportion using the PtDA is 50 % in Ottawa and 90 % in Saskatchewan, according to a commonly used rule of 10 events per independent variable, the maximum number of variables that can be included in these analyses is 66; thus, we have more than the required degrees of freedom available to fit our models. The extent of missing data will be tabulated, and characteristics of those with and without missing data will be compared. If more than 5 % missing data is observed among predictors, the use of multiple imputation will be explored. The analysis will account for clustering by provider through the inclusion of random intercepts for each provider. The model will be estimated using pseudo-likelihood or maximum likelihood in SAS v9.3.

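### Site counts behind the precision statement are not reconciled with the volumes in the setting paragraph, the Saskatchewan denominator is defined in two ways, and 90% is not a conservative value for a margin of error

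*Protocol article*

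**What the plan says.** The setting paragraph of Methods/design describes the yearly workload: "Annually, about 400 men have consultations for prostate cancer at The Ottawa Hospital Cancer Assessment Clinic and about 600 in Saskatchewan". This counts prostate cancer consultations and is not restricted to localized disease.

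The Analysis section then gives the planning counts for localized disease over two years: "We anticipate about 600 men diagnosed with localized prostate cancer over 2 years at The Ottawa Hospital Cancer Assessment Clinic and 400 in". The second figure is for men in Saskatchewan's pathway. It continues: "Using conservative estimates for proportions given the PtDA of 50 and 90 % in Ottawa and Saskatchewan, respectively", and concludes that "these sample sizes are adequate to estimate the true proportions given the PtDA with margins of error" of 4.0% in Ottawa and 2.9% in Saskatchewan, from two-sided 95% confidence intervals.

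The Saskatchewan case is described in two ways:

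- **Province-wide.** The Abstract bounds it by the province and makes every man newly diagnosed with localized disease eligible. The procedures paragraph identifies newly diagnosed men in Saskatchewan from administrative data, and the Table 1 footnote refers to all men over the two-year period.
- **Pathway only.** The opening paragraph of Methods/design bounds it by the prostate cancer surgical pathway, and the Analysis section counts men in the provincial pathway.

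The interventions paragraph of Methods/design sets an 80% threshold for prevalence of use. Below it, interventions against barriers are identified; at or above it, monitoring strategies are set up.

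**The concern.** The figures 400 and 600 appear twice with the sites exchanged, and no sentence connects the two uses. Both services are said to serve about 1 million people, so a much larger eligible share in Ottawa than in Saskatchewan needs a reason. The reader cannot tell whether the planning counts are right, transposed, or drawn from a narrower Saskatchewan population.

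The last possibility matters most. The proportion of men given the decision aid is the first outcome in Table 1 and is to be compared across the two cases. If Saskatchewan is counted among pathway men while the eligibility statement covers all newly diagnosed men in the province, the reported proportion does not describe the stated population, and the two sites may not be compared on like terms.

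Calling 90% conservative also tells the reader that the stated Saskatchewan margin is a cautious one, when it depends on an assumed proportion far from the worst case.

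**Working it through.** **Inputs.** Yearly consultations of 400 (Ottawa) and 600 (Saskatchewan), from the setting paragraph. Two-year planning counts of 600 and 400, assumed proportions of 50% and 90%, and stated margins of 4.0 and 2.9 points, from the Analysis section. The 80% threshold, from the interventions paragraph.

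**1. The plan's own figures.** Margin = 1.96 × √(p(1−p)/n).

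- Ottawa: 1.96 × √(0.50 × 0.50/600) = 4.00 points.
- Saskatchewan: 1.96 × √(0.90 × 0.10/400) = 2.94 points.

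Both agree with the article. The stated maximum of 66 variables also reproduces: (600 × 0.5 + 400 × 0.9)/10 = 660/10 = 66.

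**2. Implied eligible shares.** Two years of the yearly volumes give 2 × 400 = 800 and 2 × 600 = 1200.

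- Ottawa: 600/800 = 75%.
- Saskatchewan: 400/1200 = 33%.

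**3. If the planning counts were transposed.**

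- Ottawa, n = 400, p = 0.50: 1.96 × √(0.25/400) = 4.90 points, against 4.0 stated.
- Saskatchewan, n = 600, p = 0.90: 1.96 × √(0.09/600) = 2.40 points, against 2.9 stated.
- The total stays at 1000, as in Table 1.

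**4. Whether 90% is conservative.** For fixed n the margin is largest at p = 0.50. With the stated n = 400 in Saskatchewan:

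| Proportion given | Margin (points) |
|---|---|
| 90% | 2.94 |
| 80% | 3.92 |
| 50% | 4.90 |

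The 50% worst case is therefore 4.0 points in Ottawa and 4.9 in Saskatchewan on the stated counts, or 4.9 and 4.0 if the counts are transposed.

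**5. Sensitivity to the Saskatchewan denominator (illustration).** At the assumed 90%, 0.90 × 400 = 360 pathway men are given the decision aid. Suppose M eligible men lie outside the pathway and a fraction r of them are given it. The provincial proportion is (360 + rM)/(400 + M). Neither M nor r is in the article; the values below are assumptions chosen to show the range.

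| M | r | Provincial proportion |
|---|---|---|
| any | 0.90 | 90% |
| 50 | 0 | 360/450 = 80% |
| 200 | 0 | 360/600 = 60% |
| 200 | 1 | 560/600 = 93% |

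The choice of denominator can leave the proportion unchanged, lower it past 80%, or raise it.

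**The case against.** The strongest reply is that the two sections count different things. The setting paragraph counts all prostate cancer consultations in a year; the Analysis section counts localized diagnoses over two years, in Saskatchewan within a pathway. Arithmetically, 600 of 800 and 400 of 1200 are both possible, and the stated margins follow exactly from the stated inputs. This stands. A reader might infer that the article contradicts itself, or that its margins rest on counts known to be wrong. The documents support neither: the counts are unreconciled, not shown to be false.

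A reader might also find it telling that exchanging the counts makes both eligible shares exactly 50%. That is circular. After the exchange each two-year count equals the same site's yearly count, and N/(2N) is 50% for any N.

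Nor does a transposition shrink the stated variable budget. On the article's own way of counting, it would rise from 66 to (200 + 540)/10 = 74. Whether that rule should count men given or not given the decision aid is a separate question, which arises with or without a transposition.

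The practical effect of a transposition alone is small. The data are existing records for fixed calendar years, the final intervals will use the actual numbers, and every margin above stays below 5 points. The 80% rule acts on observed use, so the planning counts do not enter it; only the definition of the denominator does. A reader might go further and infer that a pathway-only denominator inflates Saskatchewan's proportion. The article does not say how many eligible men lie outside the pathway or how often they receive the decision aid, so no bias in a given direction is established.

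On the word conservative, 90% would be cautious if uptake above 90% were expected. The article states no such expectation; it reports anecdotally that not all men receive a decision aid, and it plans for use below 80%.

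**Conclusion.** The point holds as a correction of moderate weight, in three parts.

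- **Counts.** The site volumes reverse between the setting paragraph and the Analysis section, and the implied shares of 75% and 33% are unexplained. Transposition is a fair query. If it occurred, the margins are 4.9 and 2.4 points rather than 4.0 and 2.9, which does not overturn the claim of adequate precision.
- **Denominator.** Saskatchewan is defined both as all newly diagnosed men in the province and as men in the surgical pathway. This bears on the first outcome, its comparison with 80% and the cross-case comparison. How far and in which direction depends on the number of eligible men outside the pathway and their rate of receipt, neither of which is given.
- **Wording.** Treating 90% as conservative is wrong for a margin of error whatever the true counts are. With 400 men it gives 2.9 points, against 3.9 at the article's own 80% threshold and 4.9 at the worst case.

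The margins assume simple binomial sampling and the normal approximation, which reproduces the article's figures.

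**What to change.** 1. Check the volume counts at both sites and reconcile the setting paragraph with the Analysis section. If the planning counts were transposed, correct them; if not, add a sentence explaining how 800 and 1200 consultations become 600 and 400 eligible men.
2. Restate the margins of error on the reconciled counts, give the 50% worst case for both sites, and stop describing 90% as conservative.
3. Use one Saskatchewan denominator throughout: all men newly diagnosed with localized disease in the province, as in the Abstract and the procedures paragraph. If only pathway men can be identified, report the share of eligible men captured, and limit both the claim and the cross-case comparison to them.

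The cost is a check of existing volume counts and a few sentences of text. The quoted Saskatchewan margin will look less favourable in its worst case. If province-wide data are not readily available, reporting the captured share needs one further count.

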**Table 2 Tab2:**
[figure not shown]
Data collection tool: prostate cancer PtDA implementation study

A survey will be sent to urologists (*n* = 8–10) per site, radiation oncologists (*n* = 5-7), and nurses (*n* = 4–6) in the prostate programs to assess their use of PtDA and factors influencing use. Eligible participants will receive a mailed package that will include a cover letter with the study purpose and information on how the information will be used and the survey with a stamped pre-addressed envelope. To enhance response rates, Dillman’s approach will be used with reminders at 2, 4, and 5 weeks [39].

Interviews will be conducted with a purposeful sample of men given/not given the PtDA (and/or their partners), nurses, managers, radiation oncologists, and urologists in each program (Table 1). Men newly diagnosed with prostate cancer during the last 3 years post-PtDA implementation will be contacted by a healthcare professional from the circle of care or through the local prostate cancer support groups. Purposeful sampling will be used to identify other stakeholders having varying levels of influence in the prostate cancer programs (e.g., nurses, urologists, radiation oncologists, and managers). Prospective participants will be invited to participate in an interview by (a) announcement of the study at staff meetings, (b) hard copy posters on staff bulletin boards, and (c) email to staff (Ottawa only). A letter explaining the study will be provided to prospective participants, and written informed consent will be obtained (Additional files 1 and 2). For healthcare practitioners, a semi-structured interview guide developed using the Knowledge to Action Framework [35] will be used to explore perceptions of PtDAs, factors influencing PtDA sustained use, interventions required to overcome remaining barriers, and concurrent initiatives that may have influenced PtDA use. For men given or not given a PtDA, a semi-structured interview guide was developed to learn more about their experience with how the decision was made to treat or monitor their prostate cancer. All participants will be asked to complete demographic questions.

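### The degrees-of-freedom claim for the PtDA-receipt model counts men, and does not hold for provider characteristics, which vary only across about 13–17 physicians per site

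*Protocol article*

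**What the plan says.** The Analysis section plans a multivariable logistic model for receipt of the PtDA, fitted at each site and overall. Patient characteristics are entered "as well as provider characteristics (e.g., sex, years of experience, discipline"). Site and the interactions of these characteristics with site are added to explore site differences. Clustering is recognised: "The analysis will account for clustering by provider through the inclusion of random intercepts for each provider". Estimation is by pseudo-likelihood or maximum likelihood.

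The only argument that the data can carry these models is "a commonly used rule of 10 events per independent variable". It is applied to the expected number of men given the PtDA and gives a ceiling of 66 variables, followed by the conclusion "thus, we have more than the required degrees of freedom available to fit our models".

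The document's only indication of provider numbers is in the survey paragraph of Methods/design: "A survey will be sent to urologists (*n* = 8–10) per site, radiation oncologists (*n* = 5-7), and nurses (*n* = 4–6) in the prostate programs". The number of providers plays no part in the sufficiency argument.

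**The concern.** Sex, experience and discipline are constant within a provider. In a model with a random intercept per provider, information about such terms is limited by the number of providers. Adding men sharpens each provider's own rate of giving the PtDA, but adds no provider to compare. A rule that counts men therefore says nothing about whether these terms can be estimated well, yet the conclusion drawn from it covers the whole model.

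Two things are at stake. A reader who trusts the statement will expect precision for provider effects that the data cannot give. An analyst who trusts it may use large-sample tests for provider terms, and so report chance differences among a dozen or so physicians as determinants of PtDA use or as differences between the two cases.

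**Working it through.** **Inputs from the protocol article.** Ottawa: "We anticipate about 600 men diagnosed with localized prostate cancer over 2 years at The Ottawa Hospital Cancer Assessment Clinic". Saskatchewan: "400 in the Provincial Prostate Pathway in Saskatchewan". Use: "If the proportion using the PtDA is 50 % in Ottawa and 90 % in Saskatchewan". Physicians per site: 8–10 urologists plus 5–7 radiation oncologists = 13–17; with 4–6 nurses, 17–23. The per-site reading of all three counts gives 34–46 practitioners over two sites, which fits the roughly 40 surveyed in Table 1. If only the urologist count were per site, the total would be 25–33.

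**Assumptions.** The ICC (latent logistic scale) and the allocation of men to providers are not given. ICCs from 0.01 to 0.20 were tried.

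**1. The plan's figure.** (600 × 0.50 + 400 × 0.90) / 10 = (300 + 360) / 10 = 66. It reproduces exactly, so it counts men given the PtDA and nothing else.

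**2. The same rule on the rarer outcome.** Men not given the PtDA: 300 + 40 = 340, hence 34 variables overall. For Saskatchewan alone, 40 / 10 = 4, although the plan names four patient and three provider characteristics as examples. So 66 is also too high for patient-level terms.

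**3. Between-provider degrees of freedom** (providers − intercept − provider-level terms).
- One site, three terms: 13 − 4 = 9 to 17 − 4 = 13. The two-sided 5% critical value is 2.26 to 2.16, against 1.96 for the normal.
- Pooled model with three characteristics, site and three interactions (seven terms): 26 − 8 = 18 to 34 − 8 = 26.

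**4. Analytic size.** The two-sided tail beyond 1.96 is 8.2% for t on 9 df and 7.2% for t on 13 df.

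**5. Simulated false-positive rates**, nominal 5%, no true provider effects, random intercepts fitted as planned:

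| Estimator and reference | Setting | Rate |
|---|---|---|
| ML, normal | Ottawa, 13–17 physicians, ICC 0.01–0.20 | about 8–16% |
| ML, normal | Saskatchewan, ICC 0.05–0.20 | about 7–13% |
| ML, normal | pooled model, 26–34 physicians | about 8–15% |
| ML, normal | pooled provider-by-site interactions, 15 physicians per site, ICC 0.05–0.10 | 9–10% |
| ML, normal | Ottawa with nurses (23 providers) | about 7–11% |
| ML, t on 11 df | Ottawa, 15 physicians, ICC 0.05 / 0.10 | 7.3% / 9.0% |
| ML, t on 11 df | Saskatchewan, 15 physicians, ICC 0.05 / 0.10 | 4.3% / 6.0% |
| REML-type pseudo-likelihood, normal | all settings, ICC 0.10–0.20 | about 6–11% |
| REML-type pseudo-likelihood, normal | all settings, ICC 0.01 | about 3–8% |
| REML-type pseudo-likelihood, provider-level t | all settings, ICC 0.10–0.20 | about 3–9%, mostly near 5% |

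The pseudo-likelihood rows rest on 500 runs per setting, so each rate has a simulation standard error of about 1 percentage point (√(0.05 × 0.95 / 500) = 0.010). Omitting the random intercepts, which is not the plan, would give about 10–53%.

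**6. Precision.** Take a discipline odds ratio of 2 (log 0.693) in Ottawa, with nine urologists and six radiation oncologists, 60% and 40% of the men, and half given the PtDA:

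SE² = 1 / (600 × 0.24 × 0.25) + σ²(1/9 + 1/6), with σ² = ICC / (1 − ICC) × π²/3.

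- No clustering: SE² = 1/36, SE = 0.167.
- ICC 0.05: σ² = 0.173, SE² = 0.0278 + 0.0481, SE = 0.275; noncentral t on 11 df gives 63% power.
- ICC 0.10: σ² = 0.366, SE² = 0.0278 + 0.1015, SE = 0.360; power is 42%.

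The second term does not contain the number of men. With unlimited men the SE would still be √0.0481 = 0.219 or √0.1015 = 0.319.

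**The case against.** The plan names no Wald test, reference distribution or denominator degrees of freedom, and those details may properly sit in an analysis plan not shown. That stands. A reader might infer that the planned tests will give too many false positives, or that the intervals will be too narrow. The document does not support that: the inflation depends on a normal reference, is modest under one of the two named estimators, and is largely absent with provider-level degrees of freedom or negligible clustering. Moving from 1.96 to 2.16–2.26 widens an interval by only about 10–15%.

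A reader might also infer that the models cannot be fitted. They can: 9–13 degrees of freedom remain per site. Nor does an events-per-variable rule promise any power, and the plan claims none for provider factors.

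The physician counts come from a survey mailing, not from the administrative data, and which practitioners form the clusters is not stated. The receipt analysis is exploratory, factors in sustained use are addressed through the survey and interviews, and no decision rule hangs on a provider coefficient. All of this limits the weight of the point.

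None of it rescues the printed sentence. It concludes sufficiency for models that name provider characteristics, from a count that contains no providers. A later choice of test cannot make that reasoning right.

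**Conclusion.** The sufficiency statement does not hold for provider sex, experience, discipline and their site interactions. These terms rest on roughly 9–13 between-provider degrees of freedom per site and 18–26 in the pooled interaction model, provided the survey counts describe the clusters. Precision for them is much lower than 1,000 men suggests, whichever reference distribution is used.

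The false-positive part is conditional. With a normal reference it is a residual small-sample inflation, at most about three times nominal under maximum likelihood and smaller under pseudo-likelihood. It is far from the error of ignoring clustering, which the random intercepts prevent. The exact sizes depend on the assumed ICC and allocation of men. Since the analysis is exploratory and the correction is cheap, this should be changed, but it does not threaten the study's main descriptive results.

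**What to change.** In the Analysis section:

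- Withdraw the sufficiency statement for provider-level terms and say that they are limited by the number of providers; state the expected number and which practitioners define a cluster.
- Do not keep 66 for the patient-level terms. Use the rarer outcome: 34 variables overall and 4 in the Saskatchewan-only model, at the assumed proportions.
- Test provider terms and their site interactions with between-provider denominator degrees of freedom or a small-sample correction. Prefer REML-type pseudo-likelihood, since pseudo-likelihood is already one of the two named estimators; t on 11 df with maximum likelihood does not fully restore 5% in Ottawa.
- Keep the planned provider-by-site comparisons, but label them exploratory and imprecise, and report them with their intervals.

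The cost is a few sentences and one option in a model already planned. Intervals for provider factors become somewhat wider. No new data are needed.

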## Background

Although patient decision aids (PtDAs) are effective interventions for translating evidence for patients [1], they are not routinely used in clinical practice [2]. Our study aims to close the gap between what is currently known about PtDAs from research studies and what is done with PtDAs when they are implemented in routine clinical practice. Men with localized prostate cancer face a difficult decision because there are four main options (e.g., surgery, external radiation, brachytherapy, and active surveillance) with different potential benefits and harms. Given little evidence to indicate that one option is better than another, the chosen option should be consistent with men’s informed preferences based on weighing benefits and harms across options [3–5].

When asked to take an active role in making these difficult decisions, patients often experience decisional conflict and have unrealistic expectations [6–9]. Decisional conflict is “personal uncertainty about which course of action to take when choice among competing options involves risk, regret, or challenge to personal life values” [7–9]. Adults with unresolved decisional conflict are more likely to delay decisions, feel regret, be dissatisfied, and blame doctors for bad outcomes [10, 11]. Moreover, without effective decision support, patients may be exposed to more costly options without any better outcomes [12, 13]. Studies in Canada and the USA found that urologists and radiation oncologists often provide unbalanced information on options in favour of their own expertise, and they are not able to correctly guess men’s preferences [14, 15]. Practice variations in age-standardized rates of surgery for prostate cancer are 32 to 57 % across Ontario, Canada [16]. This variation may be unwarranted given that the best option depends on men’s preferences [17].

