*Procedures* focus on collecting clinical administrative data (clinical databases, electronic/paper-based health records) and conducting a survey and interviews (Table 1). Routinely collected administrative data sources will be reviewed to identify men newly diagnosed with localized prostate cancer for calendar years of 2011–2012 in Ottawa and 2014–2015 in Saskatchewan. Data will be retrieved on (a) their age, co-morbidities with severity, prostate cancer characteristics; (b) practitioners’ documentation of the decision-making consultation; (c) uptake of treatment or surveillance; (d) whether given the PtDA or not; and (e) level of decisional conflict (Table 2).

**Table 1 Tab1:** Proposed study data collection elements and analysis

Outcome	Participants	Data source	Analysis
Proportion given the PtDA	Men with localized prostate cancer	Clinical administrative^a^ data (~*n* = 1000)	Proportion with 95 % confidence intervals for each case study
Men’s outcomes: decisional conflict	Men with localized prostate cancer	Clinical administrative^a^ data (~*n* = 1000)	Linear regression (decisional conflict) to compare those who were given the PtDA to those who were not
Practitioner’s outcome: factors influencing PtDA use	Urologists, radiation oncologists, and nurses in prostate programs	Mailed survey (~*n* = 40)	Multivariable ordinal logistic regression analysis of practitioner’s reported use of PtDA with factors reported in the survey as covariates. Subgroup analysis will be done by types of practitioner (e.g., urologists, radiation oncologists, nurses)
Health system outcomes: uptake of treatment (including surveillance) and practitioner consultations	All men with localized prostate cancer	Clinical administrative^a^ data (~*n* = 1000)	Multinomial and binary logistic regression analysis of treatment uptake and practitioner consultations with receipt of the PtDA as main predictor, and adjusting for patient demographic and clinical characteristics.
Factors influencing PtDA implementation	Key stakeholders in each program	Individual interviews (~*n* = 30–40)	Thematic analysis guided by the Knowledge to Action Framework

^a^Clinical administrative data for all men for 2-year period after implementing the PtDA

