Outcomes between those given the PtDA and those not given it will be described at each site using mean and standard deviation (decisional conflict) and frequency and proportions (uptake of treatment, type of practitioner consulted). To estimate the effect of the PtDA on these outcomes after accounting for potential confounders, we will conduct exploratory multivariable general linear regression and binary or multinomial logistic regression at each site and overall. The analysis will adjust for patient characteristics associated with the use of the PtDA, and patient clinical and demographic characteristics potentially associated with the outcomes. To explore differences between the sites, we will include site and its interaction with the receipt of the PtDA into the model. Results will be expressed as adjusted mean differences and adjusted odds ratios together with 95 % confidence intervals.

For impact on practitioner outcomes and sustained use, we will identify remaining barriers influencing practitioner PtDA use with the survey and interview data. Audio-taped interviews will be transcribed verbatim and analyzed qualitatively by two team members using thematic analysis. We expect to reach saturation by 12 to 15 interviews in each case study [48].

The study *Timeline* is 12 months: 3 months for start-up; 5 months for collecting clinical administrative data, conducting the survey, and interviewing; 2 months for data cleaning/analysis; and 2 months for drafting case studies and disseminating findings.

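### The models for the effect of the PtDA name no provider term, although the receipt model has one and the protocol ties practitioners to both PtDA use and treatment choice

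*Protocol article*

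**What the plan says.** The Analysis section describes two sets of regression models.

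- **Receipt of the PtDA (second paragraph).** Patient characteristics and provider characteristics (sex, experience, discipline) are entered. The paragraph adds: "The analysis will account for clustering by provider through the inclusion of random intercepts for each provider". It closes by saying how the model, in the singular, will be estimated.
- **Effect of the PtDA (third paragraph).** General linear, binary or multinomial logistic models are planned, with the stated aim of allowing for potential confounders. Their adjustment set is given separately: "The analysis will adjust for patient characteristics associated with the use of the PtDA, and patient clinical and demographic characteristics" that may relate to the outcomes. Site and the site-by-receipt interaction are added. No provider covariate, provider intercept or clustered standard error is named.

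Table 1, in the health-system row, describes the models for treatment uptake and "practitioner consultations with receipt of the PtDA as main predictor, and adjusting for patient demographic and clinical characteristics". Again there is no provider term.

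On practitioners, the Background reports that "urologists and radiation oncologists often provide unbalanced information on options in favour of their own expertise". It also lists practitioners' own agenda and buy-in among the perceived influences on PtDA use.

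For the site proportions, the plan says "the proportion of men given the PtDA will be calculated for each site with 95 % confidence intervals", with planned "margins of error +4.0 % in Ottawa and +2.9 % in Saskatchewan using two-sided 95 % confidence intervals".

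**The concern.** A factor that influences both who gets the PtDA and what treatment follows is a confounder of the PtDA effect. On the protocol's own account, the practitioner may be such a factor. The plan carries the patient predictors of receipt into the outcome models but leaves the provider predictors behind. If practitioners whose patients more often get the PtDA also differ in what they recommend, part of the adjusted odds ratio for the PtDA is a practitioner effect. Men seen by the same practitioner are also not independent, so a model without provider can give intervals that are too short.

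At stake is the quantitative evidence for the second study aim, the impact of the PtDA. The Discussion intends the findings to inform decisions on scaling up. The study could report a shift in treatment uptake that is not due to the PtDA, or miss one that is.

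**Working it through.** **1. The plan's own figures.** Inputs from the Analysis section: "We anticipate about 600 men diagnosed with localized prostate cancer over 2 years at The Ottawa Hospital Cancer Assessment Clinic and 400 in the Provincial" pathway in Saskatchewan, and "Using conservative estimates for proportions given the PtDA of 50 and 90 % in Ottawa and Saskatchewan, respectively".

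Margin = 1.96 × √(p(1−p)/n).
- Ottawa: 1.96 × √(0.5 × 0.5/600) = 4.00 %, stated 4.0 %.
- Saskatchewan: 1.96 × √(0.9 × 0.1/400) = 2.94 %, stated 2.9 %.

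Both reproduce. They are independent-binomial margins, and they are sound for the stated target. Each case is bound by place and time, and the data cover all men, hence all providers there. With providers fixed, the variance is Σ nₖpₖ(1−pₖ)/n², which cannot exceed p(1−p)/n. So the point below concerns the effect models only.

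**2. The two model sets side by side.**

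| Term | Receipt model | Effect models (text) | Effect models (Table 1, health-system row) |
|---|---|---|---|
| Patient characteristics | yes | yes | yes |
| Site | yes | yes | not named |
| Provider characteristics | yes | not named | not named |
| Provider random intercept | yes | not named | not named |

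**3. When the omission matters.** In a linear model without provider, the bias is roughly Cov(provider effect on receipt, provider effect on outcome) / Var(receipt). It is zero if provider does not affect receipt, does not affect the outcome, or affects them in unrelated ways. In the last case the interval is still too short when both vary by provider.

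**4. How large it could be.** The document gives neither ICCs nor the correlation between provider effects, so these are assumptions. The simulation has 600 men, 9 providers (the protocol has 8 to 10 urologists per site), a continuous outcome with residual SD 1, and a true PtDA effect of 0.

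| ICC receipt / outcome | Correlation | Bias without provider (SD) | Actual SD / mean reported SE | Coverage without provider | Coverage with provider |
|---|---|---|---|---|---|
| 0.10 / 0.02 | 0 | −0.002 | 0.087 / 0.083 | 94.1 % | 95.7 % |
| 0.10 / 0.02 | 0.5 | 0.036 | 0.091 / 0.083 | 91.2 % | 94.5 % |
| 0.10 / 0.05 | 0 | −0.004 | 0.094 / 0.084 | 91.7 % | 95.0 % |
| 0.10 / 0.05 | 0.5 | 0.056 | 0.093 / 0.084 | 87.1 % | 95.4 % |
| 0.20 / 0.10 | 0 | 0.003 | 0.121 / 0.086 | 84.9 % | 95.1 % |
| 0.20 / 0.10 | 0.5 | 0.109 | 0.125 / 0.086 | 69.6 % | 96.0 % |

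Hand check of row 4: the half-width is 1.96 × 0.084 = 0.165. Then (0.165 − 0.056)/0.093 = 1.17 and (0.165 + 0.056)/0.093 = 2.38, so coverage is Φ(1.17) + Φ(2.38) − 1 ≈ 0.87, as simulated.

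With receipt ICC 0, leaving provider out gave 93 to 95 % coverage.

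**5. On the odds-ratio scale.** A second simulation used 1000 men, 18 urologists, no true effect, and ICCs of 0.23 (receipt) and 0.07 (treatment). Without provider, coverage was 88 % at correlation 0. At −0.3 the odds ratio was 0.88 with 77 % coverage, and at −0.5 it was 0.83 with 68 %. With provider effects the odds ratio was 1.00 to 1.01 and coverage 92 to 95 %. Only one ICC pair was tried, and its receipt ICC is above those in step 4, so this shows what strong provider variation would do and is not an expected value.

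**The case against.** - **The effect models are exploratory, in a descriptive mixed-methods case study.** True. No decision rule rests on them, which lowers the severity. They are still reported with 95 % intervals as estimates of the PtDA's effect.
- **The random-intercept sentence may be meant for every model.** It stands in the receipt paragraph, just before a sentence about a single model, and the next paragraph gives the effect models their own list. Even on the generous reading, a random intercept alone assumes provider effects are unrelated to receipt, so it need not remove this confounding.
- **The practitioner who steers treatment may be seen after the PtDA.** Men use it at home before the consultation, and nothing in the document shows that urologists hand it out. Practitioner consulted is itself an outcome, so adjusting for that person could condition on an effect of the PtDA. This stands, and it limits which provider can be used.
- **The document gives no ICCs.** This stands. A reader might infer that the PtDA effects are confounded; the document supports only that they may be. The case is strongest for treatment uptake. For decisional conflict the document gives no direct link to provider.
- **The site proportions.** A reader might also infer that the 4.0 and 2.9 margins are too narrow for lack of a design effect. The document does not support that: the target is the proportion in each bounded case, with all its providers included, and no interval method is named for the final analysis. A design effect answers a different question, namely generalising to other providers.

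**Conclusion.** The point holds for the PtDA-effect models. As written, they omit a factor that the protocol itself links to PtDA use and to treatment choice, and they make no allowance for men sharing a provider. The estimates may therefore be confounded by provider, and the intervals may be too narrow.

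The size is conditional. In the scenarios tabulated, coverage of a nominal 95 % interval runs from about 94 % down to about 70 %, with bias from about zero to 0.11 SD. This depends wholly on assumed ICCs and correlations, and harm is small if receipt does not vary by provider. The direction of any bias is unknown. The margins for the site proportions stand as stated. Severity: should-fix.

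**What to change.** Extend provider adjustment to the effect models in the Analysis text and in Table 1:

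1. Name the provider. Use one who is fixed before the PtDA is given, such as the diagnosing or referring provider, and not the practitioner consulted.
2. Use provider fixed effects, or a random intercept plus each provider's proportion of men given the PtDA.
3. Report the within-provider PtDA effect with its 95 % interval.
4. If generalising beyond the providers at these sites is intended, add a cluster-adjusted interval for the proportions as an optional sensitivity analysis.

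Cost: the receipt model already needs provider identity, so this is mainly analysis work. The data items listed under Procedures do not name the diagnosing or referring provider, so if the receipt model uses someone else, one more field must be extracted. Intervals will be somewhat wider. In Saskatchewan the within-provider comparison will be thin: at 90 % receipt, 400 × 0.10 = 40 men are without the PtDA, or 4 to 5 per urologist with 8 to 10 urologists. The random-intercept form may be the more workable one there.
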